#### 2.5.2. Secondary Outcome

The secondary endpoints are to (1) estimate the incidence rate of medication discrepancies at each transition and the discrepancy rate among the sources of information, (2) explore the impact of MR services on the medication appropriateness index (MAI) score [12], the rate of DRPs within 14 days and 30 days after discharge, 30 day mortality, ED visit rate, and readmission rate after discharge, (3) investigate the rate and acceptability of pharmacist interventions during hospitalization, and (4) explore patient satisfaction among the intervention group.

The DRP characteristics will be described using the Pharmaceutical Care Network Europe (PCNE) DRP classification [13]. The incidence rate of medication discrepancies will be calculated by dividing the number of patients with at least one discrepancy by the total number of patients in each group.

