### 2.6. Sample Size

The sample size calculation is based on the previous literature that referred to the incidence of medication discrepancies. The percentage of patients with at least one medication discrepancy varied based on ranged from 14.1% to 81.9% based on population and illness [14,15,16,17]. In a prospective French study, after proactive MR, the proportion of patients with at least one medication discrepancy decreased significantly from 45.8% to 2.07% (*p* < 0.001) [18]. Another study assessed MR in patients scheduled to undergo surgery, and the medication discrepancy rate in the intervention group decreased from 40.2% to 12.9% compared to that in the non-intervention group [19]. Using the reference rate of medication discrepancies reported in a previous study, it was estimated that 40% of the patients could experience at least one medication discrepancy, and the intervention may reduce these discrepancies by 40%. Assuming an alpha error of 5%, statistical power of 80%, and a 10% patient loss, the calculated sample size was 216 for the intervention group and 108 for the control group.

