### 2.8. Statistical Analysis

An intention-to-treat analysis will be conducted. The baseline characteristics will be summarized with descriptive statistics. Primary and secondary endpoints, except the rate and acceptability of pharmacist interventions during hospitalization, will be compared between the control and intervention groups. Categorical variables will be analyzed using the chi-square test or Fischer’s exact test, and continuous variables will be analyzed using the Student’s *t*-test or Mann–Whitney test. Data analysis will be performed after the data for the entire sample have been collected, using SAS version 9.4 (2017 SAS Institute, Cary, NC, USA) with a significance level of 0.05 and the limits of a confidence interval of 95%.

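### With groups planned at 108 versus 216 from consecutive periods, the Student's t-test named for continuous outcomes has no equal-size protection against unequal variances; naming Welch is a minor, free improvement

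*Protocol article*

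**What the plan says.** Section 2.8 (Statistical Analysis) sets one rule for all continuous variables: "continuous variables will be analyzed using the Student’s *t*-test or Mann–Whitney test". It works "with a significance level of 0.05 and the limits of a confidence interval of 95" per cent. Categorical variables have a separate rule: "Categorical variables will be analyzed using the chi-square test or Fischer’s exact test". The unequal-variance version of the t-test is neither named nor ruled out.

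Section 2.6 (Sample Size) fixes a 2:1 allocation with control as the smaller group: "the calculated sample size was 216 for the intervention group and 108 for the control group". The calculation concerns a proportion: "it was estimated that 40% of the patients could experience at least one medication discrepancy".

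The clearest continuous outcome compared between groups is in section 2.5.2, where the protocol will "explore the impact of MR services on the medication appropriateness index (MAI) score". Table 1 places this assessment at discharge. No mean or SD is given for it in either group.

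Section 2.1 makes allocation depend on calendar time: control patients first, for about four months, then intervention patients for about eight.

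**The concern.** The pooled t-test estimates one common variance, weighting each group by its size, and uses it for both means. With equal groups, errors in the two variances cancel in the standard error. At 2:1 they do not. The larger group dominates the pooled variance, while the smaller group contributes most of the uncertainty in the difference. If the smaller group is the more variable one, the standard error is too small and the interval too narrow. If it is the less variable one, the reverse holds.

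Unequal spread could arise here in two ways:

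- **Through the effect.** A score that cannot fall below zero often becomes less spread out when its mean is lowered, which would leave the larger SD in the smaller control group.
- **Through the design.** The groups are consecutive periods, not randomised arms, so case mix or practice may shift between them and change the spread in either direction, even if the service does nothing.

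At stake is whether the intervals for MAI, and for any other outcome analysed as continuous, have their stated 95% coverage.

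**Working it through.** **Inputs from the document.** Group sizes 108 and 216 (section 2.6); level 0.05 and 95% intervals (section 2.8); for the sample size, "Assuming an alpha error of 5%, statistical power of 80%, and a 10% patient loss", control rate 40% and a 40% relative reduction (section 2.6). Two-sided testing is assumed, because sidedness is not stated.

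**Step 1: reproduce the plan's own figure.** Take p1 = 0.40 and p2 = 0.40 × 0.60 = 0.24. At 2:1 the pooled rate is (0.40 + 2 × 0.24)/3 = 0.2933. For control,

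n = [1.960·√(1.5 × 0.2933 × 0.7067) + 0.842·√(0.40 × 0.60 + 0.24 × 0.76/2)]² / 0.16² = 97.2, rounded up to 98,

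with 196 for intervention. Adding 10% gives 98 × 1.1 = 107.8, so 108, and 196 × 1.1 = 215.6, so 216. The stated figures reproduce, and they rest on proportions. No variance of a continuous outcome enters.

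**Step 2: the pooled test at 2:1.** After 10% loss, 108 × 0.9 = 97.2 and 216 × 0.9 = 194.4, so use 97 and 194 (291 in all, 289 degrees of freedom). Set the intervention SD to 1 and the control SD to k. **k is an assumption; the document gives nothing from which to derive it.**

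- Variance that the pooled test uses: Vp = [(96k² + 193)/289] × (1/97 + 1/194)
- True variance of the difference: Vt = k²/97 + 1/194
- True two-sided error: 2·P(T > 1.968·√(Vp/Vt)); coverage is 1 minus this.

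Worked for k = 1.5: Vp = 1.4152 × 0.015464 = 0.02188; Vt = 0.02320 + 0.00515 = 0.02835; √(Vp/Vt) = 0.879. The interval is about 12% too short and the error is 8.5%.

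| Assumed control/intervention SD ratio | √(Vp/Vt) | Coverage of nominal 95% interval | Error rate if the means are equal |
|---|---|---|---|
| 0.67 | 1.136 | 97.4% | 2.6% |
| 0.8 | 1.076 | 96.5% | 3.5% |
| 1.0 | 1.000 | 95.0% | 5.0% |
| 1.25 | 0.929 | 93.2% | 6.8% |
| 1.5 | 0.879 | 91.5% | 8.5% |
| 2.0 | 0.816 | 89.1% | 10.9% |

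At 108 and 216 the results agree to within 0.1 percentage point. With equal groups of size n, Vp = Vt = (k² + 1)/n, so the distortion is absent; that is the protection lost at 2:1. In simulations with normal data (40,000 runs), the Welch test had an error rate of 4.7% to 5.2% at ratios of 1 to 2.

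**Step 3: does the 5% level fail, or only the interval?** The last column of the table needs unequal spreads with equal means. Two illustrations show what happens when the spread differs only because the service works. Both are assumptions, not figures for MAI.

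- Poisson counts with 40% and 24% of patients having at least one event: means −ln 0.60 = 0.511 and −ln 0.76 = 0.274, SD ratio √(0.511/0.274) = 1.36. With the effect present, the pooled interval covers 92.2% to 92.4%, against 94.7% to 94.9% for Welch. With no effect, both groups share one distribution and the pooled test rejects in 4.8% to 5.0%.
- Gamma score with SD equal to its mean, means 6 and 3.6: the pooled interval covers 90.4% to 90.6% over repeated simulations, against 94.4% to 94.6% for Welch. With no effect, the pooled interval covers about 95%.

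So on this mechanism the level holds and the interval does not.

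**The case against.** The strongest case against has four parts.

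**No evidence on spread.** A reader might infer that control is expected to be the more variable group, so that the p-values are known to be too small and in favour of the service. The document does not support this. It gives no SD, and at ratios below 1 the test is conservative. This part stands in full.

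**The level.** A reader might also infer that the 5% level fails. If the extra control spread is a product of the effect, there is none under no effect, and the level stays near 5%. This stands too. It does not rescue the interval when an effect exists. Nor does it cover a period or case-mix shift, which this before-and-after design cannot exclude and the document does not quantify.

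**Scope.** Section 2.5.2 defines discrepancy incidence as a proportion of patients and section 2.6 powers it as one, so it goes to the chi-square or Fisher test. What remains is continuous, mainly secondary outcomes such as MAI, which the protocol sets out only to explore. Mann–Whitney is a named alternative and holds its level when the two distributions are identical. It does reject too often when centres agree but spreads differ (6.4% and 9.0% in simulation at SD ratios of 1.36 and 2), but that is no reason to remove it.

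**Level of detail.** The choice of t-test version is often left to an analysis plan, and none is shown. That lowers the weight of the point. It does not remove it, because section 2.8 names a specific test that fits the stated allocation less well than its standard alternative.

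**Conclusion.** The point holds as a minor, conditional one. Under the conventional pooled reading of Student's t-test, the 108 versus 216 design leaves continuous comparisons exposed to unequal variances. The size depends wholly on an SD ratio that the document does not give: coverage of about 93% to 89% if the control SD is 1.25 to 2 times the intervention SD, 95% if the SDs are equal, and about 97% if the ratio is 0.8 to 0.67. When unequal spread is purely a consequence of the effect, only interval coverage suffers. The 5% level is lost only when spreads differ for other reasons. It is not shown that the level or the intervals will in fact fail in this trial. The discrepancy proportion and the sample size of 216 and 108 are unaffected.

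**What to change.** In section 2.8, replace Student's t-test with the Welch (Satterthwaite, unequal-variance) t-test and its confidence interval for continuous outcomes. State that it is used regardless of the observed variances, with no preliminary variance test. Mann–Whitney may stay as the rank-based alternative.

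The cost is one line of text. SAS, the named software, prints the Satterthwaite result as standard in its t-test procedure. If the variances turn out equal, the loss of power is negligible: in simulation both tests had 79.9%. No sample size changes. When the article was published the trial was still in phase 2 (section 2.10), and section 2.8 defers analysis until all data are collected, so on that timetable the choice could be fixed before any results are seen.

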### 2.9. Patient and Public Involvement

Patients or the public were not involved in the study design or conduct of this study. However, patients in the intervention group will be asked to complete a survey assessing patient satisfaction with MR services.

### 2.10. Trial Status

This trial is proceeding with phase 2. The study was registered in CRIS (Registration Number: KCT0006813; Registered 7 December 2021).

## 3. Discussion

The MERITS trial aims to evaluate the effect of a multidisciplinary MR service on medication management and patient outcomes during transitional care in older patients undergoing thoracic and cardiovascular surgeries. To the best of our knowledge, the MERITS trial is the first prospective study to evaluate the impact of implementing MR services in the Republic of Korea.

This study protocol is prone to several limitations. First, it will be conducted at a single center and target a specific population, which may limit its generalizability to other settings. Second, the MR service will be implemented only during weekdays, which may result in negative outcomes because MR may be more necessary on weekends owing to limited staff and shifts. Third, due to the before–after study design, the study cannot be blinded, which increases the risk of bias. Therefore, this study will use strategies to reduce observer bias, such as providing minimal information to the medical staff in the control group.

Although these limitations are important, the results of this study may contribute to the development of multidisciplinary MR services in cardiothoracic wards and improve patient safety during care transitions.

## Figures and Tables

**Figure 1 healthcare-11-01778-f001:**
[figure not shown]
Flow of the intervention group (Phase 2) and control group (Phase 1).

**Table 1 healthcare-11-01778-t001:** Study procedure of MERITS study.

Time Point	Study Period				
	Enrolment and Allocation	Post-Allocation			
	Admission	Hospitalization	Discharge	First Outpatient Visit (about 2 Weeks after the Discharge)	30 Days after the Discharge
**Enrolment**					
Eligibility screen	X				
Informed consent	X				
Allocation	X				
**Intervention**					
Phase 1: Control group (December 2021~)					
Phase 2: Intervention group (After phase 1 ends~)					
**Assessments**					
Baseline characteristic	X	X			
Clinical Frailty Score		X			
Medication discrepancies	X	X	X		
Number of pharmacist interventions		X			
Medication appropriate index score			X		
Patient’s satisfaction				X	
Drug-related problems				X	X
Readmission				X	X
Emergency department visit				X	X
All-cause death				X	X

“X” and arrows show the data collection time points.

## Data Availability

Not applicable.
